# Frequency of pneumothorax and haemothorax after primary open versus closed implantation strategies for insertion of a totally implantable venous access port in oncological patients: study protocol for a randomised controlled trial

**DOI:** 10.1186/s13063-015-0643-z

**Published:** 2015-03-31

**Keywords:** Venous access ports, Implantation strategies, Pneumothorax, Haemothorax

## Abstract

**Background:**

The insertion of central venous access devices, such as totally implantable venous access ports (TIVAPs), is routine in patients who need a safe and permanent venous access. The number of port implantations is increasing due to the development of innovative adjuvant and neo-adjuvant therapies. Currently, two different strategies are being routinely used: surgical cut-down of the cephalic vein (vena section) and direct puncture of the subclavian vein. The aim of this trial is to identify the strategy for the implantation of TIVAPs with the lowest risk of pneumothorax and haemothorax.

**Methods/Design:**

The PORTAS-3 trial is designed as a multicentre, randomised controlled trial to compare two implantation strategies. A total of 1,154 patients will be randomised after giving written informed consent. Patients must be over 18 years of age and scheduled for primary implantation of a TIVAP on the designated side. The primary endpoint will be the frequency of pneumothorax and haemothorax after insertion of a TIVAP by one of two different strategies. The experimental intervention is as follows: open strategy, defined as surgical cut-down of the cephalic vein, supported by a rescue technique if necessary, and in the case of failure, direct puncture of the subclavian vein. The control intervention is as follows: direct puncture of the subclavian vein using the Seldinger technique guided by sonography, fluoroscopy or landmark technique. The trial duration is approximately 36 months, with a recruitment period of 18 months and a follow-up period of 30 days.

**Discussion:**

The PORTAS-3 trial will compare two different TIVAP implantation strategies with regard to their individual risk of postoperative pneumothorax and haemothorax. Since TIVAP implantation is one of the most common procedures in general surgery, the results will be of interest for a large community of surgeons as well as oncologists and general practitioners. The pragmatic trial design ensures that the results will be generalizable to a wide range of patients.

**Trial registration:**

The trial protocol was registered on 28 August 2014 with the German Clinical Trials Register (DRKS00004900). The World Health Organization’s Universal Trial Number is U1111-1142-4420.

**Electronic supplementary material:**

The online version of this article (doi:10.1186/s13063-015-0643-z) contains supplementary material, which is available to authorized users.

## Background

Totally implantable venous access port (TIVAP) implantation was first introduced in the early 1980s by Niederhuber *et al*. [1]. Following further refinement, the technique has been adopted worldwide to create a safe and permanent venous access for chemotherapy (CHT) and/or parenteral nutrition. TIVAPs last longer, have lower infection rates and are more suitable for active patients than external central venous catheters (such as the Hickman´s catheter) [2]. The number of TIVAP insertions is constantly increasing. In Germany, 480,176 new cases of oncological diseases were diagnosed in 2010. In 2008, 80,034 TIVAP implantations were performed on in-patients in German hospitals, and it is estimated that more than 101,000 TIVAP implantations were performed in an out-patient setting in 2012 [3].

The techniques most often used for insertion of TIVAPs are surgical cut-down of the cephalic vein ((SCD) open strategy), accomplished predominantly by surgeons, and puncture of the subclavian vein ((PSV) closed strategy), performed by surgeons or interventional radiologists. The median primary success rates given in various retrospective studies and a small number of single-centre, randomised controlled trials range from 71 to 94% for SCD, and from 90 to 99% for PSV [2,4-13]. Common complications, such as kinking or dislocation of the catheter, subcutaneous haematoma, wound infection and nerve palsy, are observed with both techniques; however, specific risks are associated only with PSV, including the ‘pinch-off’ phenomenon, pneumothorax and haemothorax, which in most cases requires further treatment and often admission to hospital [14-16]. In the literature, the rate of pneumothorax and haemothorax after PSV is reported to be about 3%, ranging up to 6% in prospective studies [14-18]. In contrast, if SCD is successful there is no risk for pneumothorax or haemothorax; however, in some cases implantation via SCD is not possible, so PSV is required to implant the TIVAP. If SCD fails, a rescue technique (RT) can be executed using a guide wire, vein dilator and peel-away sheath through the cephalic vein to overcome narrow vessels or obstructions, thus avoiding PSV and its subsequent risks. Although TIVAP implantation is one of the top 50 (surgical) interventions in Germany, no multicentre trial comparing these two strategies has been performed.

## Methods/Design

### Aim of the trial

The PORTAS-3 trial, a multicenter, randomized, controlled trial comparing complication rates of open and closed implantation strategies for insertion of a totally implantable venous access port (TIVAP) in oncological patients, is a pragmatic trial that aims at comparing the open strategy (SCD and if necessary RT; if both fail, PSV) to the closed strategy (PSV) with regard to the frequency of pneumothorax and haemothorax.

### Sample size

A review of the previous literature, including our own randomised controlled trials, revealed a pneumothorax and haemothorax rate of about 3% for placement of a TIVAP by PSV; however, there is no risk if implantation by SCD is successful [14-18]. SCD was successful in 71 to 94% of cases (including the RT), therefore, about 17.5% of patients underwent PSV as a secondary implantation technique. Thus, the overall risk of pneumothorax and haemothorax for the open strategy is about 0.5% (0.175 × 0.03). Assuming a difference of 2.5%, a trial with a desired power of 0.9 and a type 1 error of 0.05 would need to include 577 patients per group to detect this difference in pneumothorax and haemothorax frequency when applying a chi-square test. No missing values for the primary endpoint are assumed, so a total of 1,154 patients have to be randomised into the two intervention groups. A Consolidated Standards of Reporting Trials (CONSORT) flow chart is provided in Figure 1.

**Figure 1 Fig1:**
[figure not shown]
**CONSORT flow chart.** cVS – classical vena section; EP – endpoint; PSV – puncture of the subclavian vein; RT – rescue technique; V – visit.

### Eligibility

#### Inclusion criteria

Only adult patients (>18 years) with an oncological disease, scheduled for primary elective TIVAP implantation on the designated side, will be included. Furthermore, all subjects will have to be able to understand the character and individual consequences of this trial, and will have to provide written informed consent before inclusion.

#### Exclusion criteria

Patients who are participating in another interventional trial which could interfere with the primary endpoint of this trial will not be admitted.

#### Subject withdrawal criteria

PORTAS-3 trial participants will be withdrawn at their own request or if, in the investigator’s opinion, continuation of the trial would be detrimental to the subject’s wellbeing. Withdrawn patients will be included in the final report of the trial to ensure complete transparency.

### Informed consent

All patients scheduled for TIVAP implantation at one of the participating centres will be screened for eligibility and will be informed about the PORTAS-3 trial during a pretreatment visit. The patients will be asked to give their informed consent after all study procedures, potential risks and benefits and the data handling have been explained to them in detail.

### Randomisation and operations for minimising bias

#### Minimisation of systematic bias

Consecutively screened and eligible patients will be included at each centre after initiation of the study. In order to achieve comparable intervention groups for known and unknown risk factors, patients will be allocated randomly to the two treatment groups in balanced permuted blocks, and stratified by centre using the central web-based software “Randomizer”, provided by the Institute of Medical Informatics, Statistics and Documentation of the Medical University of Graz. To avoid any potential for predicting the group allocation of future patients, the block length is fixed in a separate document that is withheld from the study site. In addition, persons in charge of randomisation procedures as described above will not be able to read or edit the randomisation design chosen within the software.

#### Minimisation of treatment bias

Prior to study start, staff at all participating centres will be personally trained and introduced to all study-specific procedures during a collaborative investigator meeting. In addition, all procedures will be predefined in a study-specific monitoring manual. Participating centres will be updated on a regular basis to ensure comparable treatment of patients. All centres will use the same TIVAP device (Celsite® Epoxid Port, B Braun Medical, Boulogne-Billancourt, France). Antibiotic prophylaxis will be given to patients at risk of endocarditis according to the local standards and guidelines. In other cases, peri-operative prophylactic antibiotics can be administered at the discretion of the operating surgeon.

#### Minimisation of measurement bias

Blinding of patients and surgeons is not possible due to the nature of the surgical procedures to be evaluated. However, the chosen primary endpoint is not expected to be prone to measurement bias, as pneumothorax and haemothorax are defined exclusively and can be assessed objectively [19].

### Trial treatment

Since the PORTAS-3 trial is a pragmatic trial comparing two surgical strategies, only the key features of the compared trial treatments will be predefined by the protocol. Apart from these key features, the interventions can be performed according to the individual centre’s routine and the surgeon’s standard practice. The side for TIVAP implantation will depend on surgeon’s or patient’s preference. Factors that may influence the choice of implantation side include the following: breast cancer on one side, left- or right-handedness, left or right subclavian vein is occluded by a thrombosis, patient’s wish, previous insertion of port catheter and dialysis shunt on the left or right arm.

All patients will be placed in a 5° reverse Trendelenburg position. Each patient’s neck, chest and shoulders will be prepared and draped in the customary sterile manner. Antibiotic prophylaxis will be given to patients at risk of endocarditis according to the local standards and guidelines. In other cases, peri-operative prophylactic antibiotics can be administered upon the decision of the operating surgeon. A study nurse will be present to document the intervention. The intervention will be continued in compliance with the randomisation result.

#### Intervention group A (open strategy)

Following the infiltration of local anaesthesia in sterile fashion into the skin and subcutaneous layer, a cutaneous incision will be made over the deltopectoral sulcus region to expose the cephalic vein. The cephalic vein will be ligated distally and encircled cranially with an resorbable suture. The vein will be transected ventrally (Figure 2a) and the catheter, flushed with heparinised saline, will be introduced. If simple SCD is not successful, the RT will be used as a second step. Therefore, catheter insertion will be supported by use of a guide wire (Figure 2b, c), vein dilator and peel-away sheath through the cephalic vein (Figure 2d). The guide wire and dilator will be removed, and the catheter easily introduced through the peel-away sheath, which can be removed afterwards (Figure 2e, f).

**Figure 2 Fig2:**
[figure not shown]
**Photo documentation of the rescue technique. a)** Ventral transection of cephalic vein. **b)** Introduction of a guide wire due to narrow cephalic vein. **c)** Radiograph of intravascular course of the guide wire. **d)** Introduction of vein dilator and peel-away sheath. **e)** Insertion of catheter and removal of peel-away sheath. **f)** Correctly placed catheter in cephalic vein and fixation.

Correct positioning will be controlled via X-ray, fluoroscopy (tip of the catheter in the superior vena cava just at the level of bronchial bifurcation) or intraatrial electrocardiogram. The catheter will be connected to the port chamber. Using the same incision, a subcutaneous pocket will be prepared by blunt preparation on the pectoral fascia. The port chamber will be fixed on the fascia of the pectoral muscle with three single non-absorbable sutures. Wound closure will be performed in accordance with the local standards of the trial centres. Flow for blood withdrawal and infusion will be tested via cutaneous puncture (Huber needle). To complete the procedure, the system will be blocked by means of saline with or without heparin, according to the local standards.

#### Intervention group B (closed strategy)

Guidance for the puncture by means of sonography, fluoroscopy or the landmark technique is permitted. For fluoroscopy guidance, patients receive a peripheral venous catheter on the side of the planned puncture location to administer the contrast agent and check that the subclavian vein is not obstructed by a thrombosis (roadmap technique). For sonography guidance, a standard ultrasound device can be used to visualise the subclavian vein. The landmark technique uses anatomical landmarks (clavicle, jugular fossa, and so forth) to identify the right position for PSV. Local anaesthesia will be infiltrated in sterile fashion into the skin and periosteum of the clavicle. The location of the puncture will be marked between the proximal and medial third of the clavicle. A skin incision can be performed above the puncture location.

After that, the subclavian vein will be punctured using the Seldinger technique and a guide wire will be introduced. An introducer sheath will be passed over the guide wire into the vein. The guide wire will be removed and the port catheter introduced through the introducer sheath. Correct position will be checked by X-ray, fluoroscopy or intraatrial electrocardiogram. A subcutaneous pocket will be prepared by blunt preparation on the pectoral fascia through the same incision. Alternatively, a second skin incision can be performed and a subcutaneous pocket will then be prepared bluntly on the pectoral fascia. The port chamber will be fixed on the fascia of the pectoral muscle with three single non-absorbable sutures. Wound closure will be performed in accordance with the local standards of the trial centres. Correct position of the port catheter will be checked again through X-ray or fluoroscopy (tip of the catheter in the superior vena cava just at the level of bronchial bifurcation). Flow for blood withdrawal and infusion will be tested via cutaneous puncture (Huber needle). To complete the procedure the system will be blocked by means of saline, with or without heparin, according to local standards.

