### Primary and secondary endpoints

#### Primary endpoint

The primary endpoint will be the frequency of post-interventional pneumothorax and haemothorax. Pneumothorax and haemothorax will be defined as the presence of air or blood in the pleural space, respectively. The rate of pneumothorax and haemothorax will be assessed two hours post-implantation by means of a chest X-ray (in inspiration) by the responsible physician if PSV was performed. In the event that SCD with or without RT is successful, a chest X-ray will be performed only in patients with suspicion or symptoms of pneumothorax or haemothorax (for example dyspnoea), since SCD has no associated risk of these conditions. A copy of the post-operative pneumothorax and/or haemothorax control radiograph will be saved in digital form, using radiological image viewing software (such as Centricity®, GE Healthcare, Buckinghamshire, United Kingdom), or a copy of the original radiograph will be archived. The presence of pneumothorax and haemothorax will be documented in the case report form (CRF). At follow-up visit three on day 30, the study nurse will also ask the patient about further post-operative occurrence of pneumothorax and haemothorax and check the patient’s documents for further diagnostic and treatment procedures in this regard.

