##### Thirty-day morbidity

This is defined as the occurrence of any of the complications listed in Table 1, known as possible peri- and post-operative complications of TIVAP implantation leading to deviation from the expected post-operative course. Peri- and post-operative complications of port implantation will be recorded with tick boxes in the CRF on the day of operation and at visit three (30 days after operation, by telephone questionnaire) by the surgeon and/or study nurses. All complications will be rated according to the Clavien-Dindo classification of surgical complications (Table 2) [20]. In the event of not being able to talk to the patient at the 30-day telephone interview, the study nurse will contact the relatives or family physician to ask them for information regarding the follow-up criteria.

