**Table 1 Tab1:** **Definitions of peri- and post-operative complications**

**Complication**	**Definition**
Intra-operative lesion of nerves	Clinical diagnosis and/or EMG findings
Dislocation of the catheter and/or the port chamber	Radiological finding
Incompatibility of contrast agent	Any allergic reaction against a contrast agent needing medical treatment with drugs
Thrombosis	Sonographic findings and/or phlebography
Post-operative bleeding	Clinical diagnosis during reoperation
Haematoma	Clinical diagnosis, no reoperation necessary
Disconnection or breakage of the catheter	Radiological findings, findings after explantation
Extravasation of injected fluid	Radiological findings and/or clinical diagnosis
Wound infection	Clinical diagnosis, wound has to be reopened and/or antibiotic treatment
Catheter sepsis	Two or more of the following symptoms:
	Temperature over 38.3°C or under 36°C;
	Heart rate over 90 beats per minute;
	Respiration rate over 20 breaths per minute, PaCO_2_ < 32 mmHg (spontaneous breathing) or PaO_2_/FiO_2_ < 200 mmHg (mechanical ventilation);
	Total peripheral WBC count >12 G/L or WBC <4.0 G/L or >10% immature neutrophils (bands), regardless of total peripheral WBC count;
	Plasma C-reactive protein >2 SD above normal value and positive findings in bacteriology of the port catheter pike
Cutaneous necrosis	Clinical diagnosis and/or histological finding
Pinch-off phenomenon	Radiological findings and/or clinical diagnosis

EMG: electromyography; PaCO2: partial pressure of carbon dioxide; PaO2: partial pressure of oxygen; FiO2: fraction of inspiratory oxygen; mmHg: millimetres of mercury; WBC: white blood cells.

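### Dislocation counts only as a radiological finding, yet imaging after port fixation is required only when puncture is performed, so silent dislocations will be found mainly after puncture

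*Protocol article*

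**What the plan says.** **Definition.** Under *Thirty-day morbidity* the endpoint is set out thus: "This is defined as the occurrence of any of the complications listed in Table 1". The same sentence adds that these are complications that make the course after surgery deviate from what was expected. One row of Table 1 is "Dislocation of the catheter and/or the port chamber", and its definition column gives a radiological finding and nothing else. The rows for extravasation and pinch-off also accept a clinical diagnosis.

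**Closed arm.** Under *Intervention group B (closed strategy)* there are two position checks. The first comes before the pocket is made: "Correct position will be checked by X-ray, fluoroscopy or intraatrial electrocardiogram". The second comes after pocket, fixation and wound closure: "Correct position of the port catheter will be checked again through X-ray or fluoroscopy". ECG is not an option at the second check.

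**Open arm.** Under *Intervention group A (open strategy)*, in the text after Figure 2, there is one check: "Correct positioning will be controlled via X-ray, fluoroscopy", with intraatrial ECG as a further alternative. It is described before the catheter is connected and the chamber fixed. After fixation and closure only flow is tested.

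**Two-hour film.** Under *Primary endpoint*, pneumothorax and haemothorax are "assessed two hours post-implantation by means of a chest X-ray (in inspiration) by the responsible physician if PSV was performed". After successful cut-down, with or without the rescue technique, a chest X-ray is taken only on suspicion or symptoms of those two conditions.

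**Later follow-up and analysis.** Visit three is a telephone questionnaire. *Further analyses* has secondary variables tabulated descriptively, with descriptive P values and 95% confidence intervals between groups.

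**The concern.** An event defined by an image can be counted only in a patient who is imaged. Here the required imaging after fixation follows the technique performed and so differs sharply between the arms. A tip that moves without symptoms during connection, pocket preparation or fixation can be seen on a required image after puncture. After successful cut-down it comes to light only if something else prompts imaging.

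The *Background* lists catheter dislocation among complications seen with both techniques, so readers will take a difference in its frequency as a real contrast between strategies. If part of that difference comes from looking harder in one arm, puncture will seem to carry more dislocation, and more 30-day morbidity, than it does. The distortion would favour the strategy that the *Discussion* expects to be better on the primary endpoint.

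**Working it through.** **Plan's own figure.** With 3% versus 0.5%, two-sided α = 0.05, power 0.9 and a chi-square test without continuity correction:

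n = [1.960 × √(2 × 0.0175 × 0.9825) + 1.282 × √(0.03 × 0.97 + 0.005 × 0.995)]² / 0.025² = 577 per group after rounding up. This reproduces *Sample size*; the point does not dispute it and uses 577 only as the arm size.

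**Inputs**
- s, the share of the open arm that ends with puncture: 17.5% (*Sample size*). The quoted cut-down success of 71 to 94% gives a range of 6 to 29%.
- f, the share of the closed arm that may finish by cut-down: the *Discussion* describes the closed strategy as puncture, with cut-down if puncture fails. The *Background* gives puncture success of 90 to 99%, so f is 1 to 10%.
- d, the true rate of silent dislocation present by the last required image: not in the article, so assumed, and set equal in both arms.

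**Step 1: patients with no required image after fixation**
- Open: 577 × (1 − 0.175) = 476. Range: 577 × 0.71 = 410 to 577 × 0.94 = 542.
- Closed: 577 × 0.01 = 6 to 577 × 0.10 = 58, if those who finish by cut-down are not imaged. The article does not say whether a failed puncture counts as puncture performed, so this is an upper reading.

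**Step 2: where detected silent dislocations come from.** Assume that every one on a required image is recognised and recorded and that none is found otherwise. Detection is then (1 − f) in the closed arm and s in the open arm. The closed share of those detected is (1 − f)/(1 − f + s), and the apparent closed-to-open ratio is (1 − f)/s.

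| s | f | Closed share | Apparent ratio |
|---|---|---|---|
| 17.5% | 0 | 1/1.175 = 85% | 5.7 |
| 17.5% | 10% | 0.90/1.075 = 84% | 5.1 |
| 6% | 0 | 1/1.06 = 94% | 16.7 |
| 29% | 0 | 1/1.29 = 78% | 3.4 |
| 29% | 10% | 0.90/1.19 = 76% | 3.1 |

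These ratios arise with no true difference between the strategies.

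**Step 3: absolute size under assumed d.** With s = 17.5%, the expected detected numbers are 577 × d × (1 − f) versus 577 × d × s, and the spurious difference is d × (1 − f − s). Values for f = 0, with f = 10% in brackets:

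| Assumed d | Closed | Open | Difference, percentage points |
|---|---|---|---|
| 0.5% | 2.9 (2.6) | 0.5 | 0.41 (0.36) |
| 1% | 5.8 (5.2) | 1.0 | 0.83 (0.73) |
| 2% | 11.5 (10.4) | 2.0 | 1.65 (1.45) |
| 3% | 17.3 (15.6) | 3.0 | 2.48 (2.18) |

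The values of d are illustrations, not estimates.

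**The case against.** **The repeat check is part of the operation.** It precedes the flow test, and a misplaced tip seen then can be put right before the patient leaves. The article does not say that such a tip is recorded as a Table 1 dislocation. This stands for the repeat check. It does not apply to the two-hour film, which is taken after the procedure has ended.

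**Morbidity is limited to events that change the expected course.** A silent shift without consequence need not count. This stands and narrows the effect on the composite. It leaves the silent dislocations that lead to action once seen, and the separate tabulation of dislocation.

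**The open arm is imaged too.** *Primary success rate* expects radiographic control of the tip in both arms, so a reader who infers from the ECG option that open-arm patients may have no image at all goes too far. However, an intra-operative image satisfies that definition, and it may precede fixation. The asymmetry after fixation remains.

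**The closed arm is not fully imaged.** A reader might infer that every closed-arm patient has a post-fixation image. Cut-down after failed puncture means that this is not established, which is why f is carried above. The conclusion hardly changes.

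**The direction is not certain.** Early correction in the closed arm could prevent later symptomatic dislocations there, and incidental imaging could find some open-arm cases. Both work against the bias, and neither can be quantified from the article.

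**The stakes are limited.** Dislocation is one of 12 Table 1 complications in a descriptively analysed secondary endpoint. This stands.

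**Conclusion.** The point holds as a matter of unequal detection. The definition needs an image, and after fixation an image is required only where puncture was performed. About 476 of 577 open-arm patients (410 to 542 over the article's success range) have no required post-fixation image, against roughly 6 to 58 in the closed arm. If true silent rates are equal, about 84 to 85% of the silent dislocations detected would come from the closed arm at 17.5% conversion, and about 76 to 94% over the article's ranges. That rests on complete recording of what the required images show and no other detection.

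A reader might infer that the 30-day morbidity comparison is bound to come out against puncture by a known amount, or that the trial's main result is affected. The article supports neither. It gives no dislocation rate and no silent share, the qualifier in the morbidity definition may exclude some events, and early correction may partly offset the effect. The confirmatory test and the sample size do not depend on dislocation. The supported conclusion is that the descriptive comparison of dislocation and 30-day morbidity can be biased against the closed strategy by an unknown amount, and that the data as planned may not let anyone tell how much. It merits a change because the remedy is nearly free.

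**What to change.** - Add one CRF item for each dislocation: found on a protocol-required routine image, or because of symptoms or malfunction; and whether it was corrected.
- Report dislocation by mode of detection in each arm.
- Show 30-day morbidity twice, with and without dislocations found only on routine imaging. State that the first version is open to detection bias against puncture and that the second may favour puncture through early correction.

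Simply removing routinely found dislocations from the composite would not be a neutral remedy. Some closed-arm events would have become symptomatic had they not been found and corrected, while their open-arm counterparts would go on to cause symptoms and be counted. Because staff are unblinded, the label for mode of detection is also partly a judgement; reporting both versions keeps that visible.

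The cost is one CRF item and one extra table line. Imaging and care are unchanged. The item is best added while recruitment is under way, because the reason for an image may not be recoverable afterwards.
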